**HIV Antiretroviral Medications and Adherence**

| ***Interviewer reads:*** “Now I have questions about medications you may take for HIV care or treatment. By HIV medications I mean HIV antiretroviral medications, cotrimoxazole, Bactrim, or Septrim. Please do not include multivitamins or medications for TB or other infections.” |
| --- |

G1. Do you take medication for your HIV?

_____ 0. No *Skip to G10*

_____ 1. Yes

*_____-1. Don’t know*  *Skip to G10*

*_____-2. Refused*  *Skip to G10*

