**Study design and locations**

Study design

This project will be a longitudinal group-randomized trial, randomized at the clinic level. Six HIV care and treatment clinics in each of three countries (Kenya, Namibia, and Tanzania) will participate (18 clinics total). The six clinics in each country are matched based on size, health care provider/patient ratio, and services provided (e.g., number of health care providers, size of clinic and number of HIV-positive patients seen, level of care provided). Intervention status was randomly assigned to one clinic in each matched pair.

Health care providers and staff will be trained to deliver the HIV prevention interventions to all patients in clinics randomly assigned as intervention sites. In the comparison site clinics, providers and staff will deliver their usual standard of care services. Following completion of the project, health care providers in the comparison clinics will be trained to deliver the HIV prevention interventions.

A measurement cohort of 3600 HIV-positive patients will be randomly recruited to participate from each of the 18 clinics in the 3 participating countries (n=200 per clinic). Participants in the intervention and comparison groups will be assessed at 3 time points: Baseline (enrollment), 6-, and 12-months. After participants have completed the baseline assessments, the prevention interventions will be implemented by health care providers and lay counselors in the intervention clinics.

Assessment of patients will include completion of an interviewer-administered questionnaire. At each assessment, trained interviewers will ask participants about their sexual behavior, STI symptoms, pregnancy status and intentions, contraceptive use, alcohol use, HIV ARV medication adherence and adherence to co-trimoxazole prophylaxis, partner HIV testing history and HIV status, mood and perceived social support (see Appendix H). To the extent possible, participants will be interviewed following a routine HIV clinic visit in order to reduce burden on patients.

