**Objectives**

1. To evaluate the effectiveness of integrating an HIV prevention intervention package into routine care and treatment of HIV positive patients in HIV clinics in resource-limited settings. The impact of the intervention package on the following outcomes will be assessed:

Behavioral

- Risky sexual behaviors (i.e., unprotected sex, number of sex partners)
- HIV testing of partners
- Disclosure of HIV status to sex partners
- Alcohol use
- HIV ARV medication adherence

Biologic

- Unintended pregnancies
- STIs (i.e., urethral discharge. Vaginal discharge will not be examined as an outcome due to the increased likelihood of overestimating STIs in HIV-positive women with candidiasis or bacterial vaginosis.)

Service Delivery

- Family planning counseling (e.g., safer pregnancy) and services (e.g., contraceptive pills and injections dispensed, safer pregnancy discussions, PMTCT referrals)

2. To assess the feasibility and acceptability of integrating a prevention intervention package into the routine care and treatment of HIV-positive patients in resource-limited HIV clinics in three sub-Saharan African countries.

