**Hypotheses**

Project hypotheses focus on the effectiveness of the prevention intervention package on behavioral outcomes, biologic outcomes, and delivery of services in the HIV care and treatment settings. Intervention clinics will integrate the HIV prevention intervention package into routine care of HIV-positive patients; comparison clinics will provide standard of care to HIV-positive patients.

Compared to participants attending comparison HIV clinics, participants at intervention clinics will be more likely over a 12-month period to report or show a(n):

Behavioral

- Decrease in unprotected vaginal and anal sex
- Decrease in number of sex partners
- Increase in number of sex partner(s) getting an HIV test
- Increase in disclosure of HIV status to sex partner(s)
- Decrease in alcohol use
- Increase in adherence to HIV antiretroviral medications

Biologic

- Decrease in unintended pregnancy or partner pregnancy
- Decrease in STIs (i.e., urethral discharge)

Service Delivery

Compared to the comparison clinics, the intervention clinics will:

- Provide more family planning counseling (e.g., safer pregnancy) and services (e.g., contraception) to HIV-positive women and their partners

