***[IF PATIENT TOOK ONLY A PORTION OF A DOSE ON ONE OR MORE OF THESE DAYS, PLEASE REPORT THE DOSE(S) AS BEING MISSED.]***

|  | How many doses did you **miss**…  By dose I mean each time you take medications during the day. | |
| --- | --- | --- |
| **Step 1**  Abbreviations / Drug names | **Step 2**  In the last 4 days | **Step 3**  In the last 30 days |
| 1. **__________________________**   ***_____*** *-1. Don’t know*  ***_____*** *-2. Refused* | ____________ doses  ***_____*** *-1. Don’t know*  *_____ -2. Refused* | ____________ doses  ***_____*** *-1. Don’t know*  *_____ -2. Refused* |
| 1. **____________________________**   ***_____*** *-1. Don’t know*  ***_____*** *-2. Refused* | ____________ doses  ***_____*** *-1. Don’t know*  *_____ -2. Refused* | ____________ doses  ***_____*** *-1. Don’t know*  *_____ -2. Refused* |
| 1. **____________________________**   ***_____*** *-1. Don’t know*  ***_____*** *-2. Refused* | ____________ doses  ***_____*** *-1. Don’t know*  *_____ -2. Refused* | ____________ doses  ***_____*** *-1. Don’t know*  *_____ -2. Refused* |
| 1. **____________________________**   ***_____*** *-1. Don’t know*  ***_____*** *-2. Refused* | ____________ doses  ***_____*** *-1. Don’t know*  *_____ -2. Refused* | ____________ doses  ***_____*** *-1. Don’t know*  *_____ -2. Refused* |

G5. Most medications need to be taken on a schedule, such as ‘2 times a day’ or ‘every 12 hours.’ How closely did you follow your specific schedule over the last 4 days?

_____ 0. Never

_____ 1. Some of the time

_____ 2. About half of the time

_____ 3. Most of the time

_____ 4. All of the time

*_____-1. Don’t know*

*______-2. Refused*

G6. *[****Interviewer:*** *Show the participant the drawing and ruler while you are reading the directions.]*

| ***Interviewer Reads:*** “I want to ask about your experience taking your HIV medicines over the past 30 days. Please look at this drawing and ruler. The first cup on the left is empty and represents taking none of your antiretroviral doses in the past 30 days. The last cup on the right is full and represents taking all of your antiretroviral doses in the past 30 days. Using these pictures as a guide, please show me on the line how much of your antiretroviral medicine you took in the past 30 days. For example, if you took half of your doses during the past 30 days, you would select number 5.” |
| --- |

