**ALL**

**10**

**
[figure not shown]
**

*_____-1. Don’t know*

*_____-2. Refused*

G7. When was the last time you missed any of your medications?

_____ 5. Within the past week

_____ 4. 1-2 weeks ago

_____ 3. 2-4 weeks ago

_____ 2. 1-3 months ago

_____ 1. More than 3 months ago

_____ 0. Never skip medications *Skip to H1 in next section*

*_____-1. Don’t know*

*_____-2. Refused*

G8. Some people find that they may go without pills for more than 2 days at a time. In the last 6 months, have you ever not taken or missed your medications for more than 2 days at a time?

_____ 0. No  Go to H1

_____ 1. Yes

*_____-1. Don’t know*

*_____-2. Refused*

G9. Here is a list of possible reasons why you may miss taking your medications for more than 2 days at a time. In the last 6 months, have you missed taking your HIV medications for more than 2 days at a time because you:

|  | **No** | **Yes** | *Don’t know* | *Refused* |
| --- | --- | --- | --- | --- |
| 1. Were away from home? | 0 | 1 | *-1* | *-2* |
| 1. Were busy with other things? | 0 | 1 | *-1* | *-2* |
| 1. Simply forgot? | 0 | 1 | *-1* | *-2* |
| 1. Had too many pills to take? | 0 | 1 | *-1* | *-2* |
| 1. Wanted to avoid side effects? | 0 | 1 | *-1* | *-2* |
| 1. Did not want others to notice you taking medication? | 0 | 1 | *-1* | *-2* |
| 1. Had a change in daily routine? | 0 | 1 | *-1* | *-2* |
| 1. Felt like the drug was toxic/harmful? | 0 | 1 | *-1* | *-2* |
| 1. Fell asleep/slept through dose time? | 0 | 1 | *-1* | *-2* |
| 1. Felt sick or ill? | 0 | 1 | *-1* | *-2* |
| 1. Felt depressed /overwhelmed? | 0 | 1 | *-1* | *-2* |
| 1. Had problems with taking pills at specified times (with meals, on empty stomach, etc.)? | 0 | 1 | *-1* | *-2* |
| 1. Ran out of pills? | 0 | 1 | *-1* | *-2* |
| 1. Felt good? | 0 | 1 | *-1* | *-2* |
| 1. Did not have enough food to take with pills? | 0 | 1 | *-1* | *-2* |
| 1. Could not get transportation to the clinic to pick up more pills? | 0 | 1 | *-1* | *-2* |

*[After completing G9, go to H1 in next section.]*

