**Only for Participants NOT taking HIV Medications**

G10.

| ***Interviewer Reads:*** “The following are some reasons other people have told us why they are **not** currently taking any HIV medications. After I read you each reason, please tell me if it describes you.” |
| --- |

|  | **No** | **Yes** | *Don’t know* | *Refused* |
| --- | --- | --- | --- | --- |
| 1. No doctor or other medical provider has ever offered HIV medications to me. | 0 | 1 | *-1* | *-2* |
| 1. A medical provider offered them to me, but I choose not to take HIV medications at this time. | 0 | 1 | *-1* | *-2* |
| 1. I discussed taking HIV medications with my medical provider, but he/she did not think it was a good idea for me now. | 0 | 1 | *-1* | *-2* |
| 1. My CD4 (T-cell) count is too high for me to take HIV medications. | 0 | 1 | *-1* | *-2* |
| 1. I tried HIV medications, but there were too many unpleasant side effects. | 0 | 1 | *-1* | *-2* |
| 1. I tried HIV medications, but they were not effective for me. | 0 | 1 | *-1* | *-2* |
| 1. I tried HIV medications, but they were too difficult to take as prescribed. | 0 | 1 | *-1* | *-2* |
| 1. I cannot afford them. | 0 | 1 | *-1* | *-2* |
| 1. Is there any other reason why you are not currently taking any HIV medications?   ***If yes*:** Reason __________________________ | 0 | 1 | *-1* | *-2* |

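### Section G of the patient questionnaire does not separate cotrimoxazole from ARVs at its gate or in G2, G5 and G7–G9, so those answers are pooled and cotrimoxazole-only patients are misrouted

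*Protocol*

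**What the plan says.** The outcome is specific to antiretrovirals. The Objectives list "HIV ARV medication adherence", and the Hypotheses predict "Increase in adherence to HIV antiretroviral medications". The Variables section lists HIV medication adherence among the primary outcome variables, although the sample size rests on any unprotected sex in the past 3 months.

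Asking about cotrimoxazole is deliberate. Study design and locations says that interviewers will ask about "HIV ARV medication adherence and adherence to co-trimoxazole prophylaxis", naming two things side by side. The description of the questionnaire under Study instruments also counts co-trimoxazole prophylaxis among the HIV medications to be asked about.

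Appendix H, section G, then reads the patient one definition, "By HIV medications I mean HIV antiretroviral medications, cotrimoxazole, Bactrim, or Septrim", followed directly by the gate "G1. Do you take medication for your HIV". A Yes leads into G2–G9. No, Don't know and Refused all go to G10, whose block is headed "Only for Participants NOT taking HIV Medications". Within G2–G9, G6 tells the patient "please show me on the line how much of your antiretroviral medicine you took in the past 30 days", while G8 asks "In the last 6 months, have you ever not taken or missed your medications for more than 2 days at a time".

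**The concern.** One gate is doing two jobs. It has to admit anyone taking either drug, so that cotrimoxazole adherence can be recorded, and it also has to identify the people whose ARV adherence is the outcome. Under the definition read out, it does only the first.

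Two things follow:

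- For a patient on both drugs, a missed cotrimoxazole dose counts as a miss in every item that speaks only of medications or HIV medications.
- A patient on cotrimoxazole alone goes through an ARV-adherence block and is kept out of the questions on why he or she is not on treatment.

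At stake are the cleanness of several adherence items and the completeness of G10. The powered outcome is not affected.

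**Working it through.** **Step 1. Class each item by what it can distinguish (Appendix H, section G).**

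| Item | Content | Can ARVs be separated? |
|---|---|---|
| G1 | Gate, combined definition | No |
| G2 | Start date | No, one date for any HIV medication |
| G3 | Regimen list | Yes, one row per drug, with its purpose |
| G4 | Missed doses, last 4 and 30 days | Yes, one row per drug, matched to G3 |
| G5 | Keeping to schedule, last 4 days | No |
| G6 | 30-day visual scale | Opens with HIV medicines, but anchors and rating refer to antiretrovirals |
| G7 | Last time anything was missed | No |
| G8 | Gap of more than 2 days, last 6 months | No |
| G9 | Reasons for such gaps | No |

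Of the six items G4–G9, four are pooled (G5, G7, G8, G9). G9 collects reasons, so of the five items that measure adherence itself, three are pooled (G5, G7, G8) and two can be made ARV-specific (G4, G6).

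**Step 2. Trace three patients.**

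- *ARVs only:* Yes at G1, then G2–G9. All answers refer to ARVs.
- *ARVs and cotrimoxazole:* Yes at G1, then G2–G9. G4 and G6 are usable; G2, G5 and G7–G9 are pooled.
- *Cotrimoxazole only:* Yes at G1 under the definition. G6 then asks for a rating of ARV doses from someone who takes none, offering only Don't know and Refused as ways out. Every exit from G7, G8 and G9 leads to section H, so G10 is never asked. G10 contains reasons that suit this patient, such as a CD4 count too high for treatment.

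**Step 3. Count the exposure.**

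Inputs: 18 clinics, 200 patients per clinic, about 100 of them not on ARVs (Estimated number of participants). The plan's total reproduces: 18 × 200 = 3,600.

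- Not on ARVs at baseline: 18 × 100 = 1,800.
- Let c be the share of these taking cotrimoxazole. The protocol does not give c, so a range is shown.
- Misrouted patients = 1,800c. Their share of those entering G2–G9 = 1,800c / (1,800 + 1,800c) = c / (1 + c), if every ARV patient answers Yes at G1.

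| Assumed c | Misrouted at baseline | Share of G2–G9 respondents |
|---|---|---|
| 25% | 450 | 0.25/1.25 = 20% |
| 50% | 900 | 0.50/1.50 = 33% |
| 75% | 1,350 | 0.75/1.75 = 43% |
| 100% | 1,800 | 1/2 = 50% |

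These counts measure routing, not bias. The number of ARV patients who also take cotrimoxazole, and so give pooled answers, is likewise not stated.

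**The case against.** The strongest reply is that the outcome can be rescued from the form as it stands. G3/G4 give missed doses by drug. The G6 rating is about antiretrovirals. ARV status is recorded independently of G1 by screening question 8 (Appendix C) and by chart item 5 at each assessment (Appendix P), and chart item 10 adds ARV dispensing records where available. Cotrimoxazole-only respondents can therefore be filtered out. Which items form the outcome, and in whom, is commonly left to a statistical analysis plan. G10 appears in no objective or hypothesis. All of this stands.

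It also disposes of a stronger inference that a reader might draw: that ARV adherence cannot be measured in this trial, or that a cotrimoxazole effect would be reported as an ARV effect. That would require basing the outcome on G5, G7 or G8 rather than G4 and G6, or analysing everyone who answered the section. Nothing in the protocol says either will be done.

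What the reply does not reach is the pooling itself. G4 covers 30 days by drug, but nothing by drug corresponds to the schedule-keeping in G5, the older categories of G7, or the six-month window of G8 and G9. Nor can a G10 that was never asked be recovered.

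A second reply is that cotrimoxazole-only patients might answer No at G1. The definition is read just before it, so that would be a departure from the text. It would also lose the cotrimoxazole adherence that the protocol intends to record, because G3 and G4 would be skipped.

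**Conclusion.** The defect is real and limited. Including cotrimoxazole is not the fault; failing to separate it at G1 and in G2, G5 and G7–G9 is. Patients on both drugs give answers to G5, G7, G8 and G9 that no analysis can divide into ARV and cotrimoxazole adherence. Patients on cotrimoxazole alone are asked an inapplicable G6 and lose G10.

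An ARV-specific outcome remains available from the ARV rows of G4 and from G6 among patients on ARVs, so the listed outcome is weakened in its supporting items rather than lost. At most about 1,800 participants can be misrouted at baseline, and 450 to 1,350 on an assumed cotrimoxazole share of 25% to 75%. These figures assume that the planned half-and-half enrolment by ARV status is met and that patients follow the definition read to them.

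**What to change.** Before fielding, change section G as follows:

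- Split G1 into G1a (taking ARVs?) and G1b (taking cotrimoxazole, Bactrim or Septrim?).
- Ask G3 and G4 if either is Yes, one row per drug.
- Ask G2 and G5–G9 only if G1a is Yes, worded for ARVs throughout.
- Send everyone whose G1a is not Yes to G10, worded for ARVs, but after G3/G4 where G1b is Yes. Sending them straight to G10 would lose the cotrimoxazole adherence that the protocol wants from patients not on ART.
- State that the ARV-adherence outcome uses the ARV rows of G4, and G6, among participants on ARVs as confirmed by chart item 5.

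The cost is one added item and re-translation of a few lines. The protocol already plans to pilot and revise the questionnaire (Study timeline; Data collection, pilot study), so this needs no new step. The trade-off is that G5 and G7–G9 would no longer cover cotrimoxazole, whose adherence would come from its own G4 row.

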**Only for Participants taking HIV Medications**

G2. When did you first start taking HIV medications?

[ dd / mm / yyyy ]

*_____-1. Don’t know*

*_____-2. Refused*

**G3.**

| ***Interviewer reads:*** “Most people with HIV have many pills to take at different times during the day. Many people find it hard to always remember their pills:   - Some people get busy and forget to carry their pills with them. - Some people find it hard to take their pills according to all the instructions,   such as “with meals” or “on an empty stomach,” “every 8 hours,” “with plenty of fluids.”   - Some people decide to skip pills to avoid side effects or to just not be taking pills that day.   We need to understand how people with HIV are really doing with their pills. Please tell us what you are **actually** doing. Don’t worry about telling us that you don’t take all your pills. We need to know what is really happening, not what you think we “want to hear.”  We would like to know what HIV medications you are taking now. Please tell me   - the names of the HIV medications you have been taking in the last 30 days, - what the medication is for, - how many pills you are supposed to take each time, and - how many times per day you are supposed to take each medication. Each time you take medications during the day is a dose.   Please tell me the name of the HIV medications.” |
| --- |

| **G3. HIV Medication Name** | **What is this medication for?** | **# pills each time (pills each dose)** | **# times per day (doses per day)** |
| --- | --- | --- | --- |
| a. **______________________**  *_____ -1. Don’t know*  *_____ -2. Refused* | **_________________**  *_____ -1. Don’t know*  *_____ -2. Refused* | **___________**  *__-1. Don’t know*  *__ -2. Refused* | **___________**  *__-1. Don’t know*  *__ -2. Refused* |
| b. **______________________**  *_____ -1. Don’t know*  *_____ -2. Refused* | **_________________**  *_____ -1. Don’t know*  *_____ -2. Refused* | **___________**  *__-1. Don’t know*  *__ -2. Refused* | **___________**  *__-1. Don’t know*  *__ -2. Refused* |
| c. **______________________**  *_____ -1. Don’t know*  *_____ -2. Refused* | **_________________**  *_____ -1. Don’t know*  *_____ -2. Refused* | **___________**  *__-1. Don’t know*  *__ -2. Refused* | **___________**  *__-1. Don’t know*  *__ -2. Refused* |
| d. **______________________**  *_____ -1. Don’t know*  *_____ -2. Refused* | **_________________**  *_____ -1. Don’t know*  *_____ -2. Refused* | **___________**  *__-1. Don’t know*  *__ -2. Refused* | **___________**  *__-1. Don’t know*  *__ -2. Refused* |

G4.

| ***Interviewer Reads:*** “The next section of the questionnaire asks about the medications that you may have **missed** taking over the last four days and last 30 days.” |
| --- |

*[****Interviewer:*** *Complete the table below, using one line for each medication the patient is taking. Write in the medications from the previous question. The same medication should be repeated in the same place on both this question and the previous question (for instance in ‘a’ for both questions). For each medication, ask the patient how many DOSES he or she missed in the last 4 days, and in the last 30 days. If patient did not miss any doses, write a zero (0) in the box. If the patient missed ALL their doses, write the number that they missed.*

*Note that the table asks about DOSES, not PILLS.*

*DOSES are the number of times the patient takes their pills during the day. For example, if they take pills in the morning and the evening they have 2 DOSES per day. They may take 1 pill, 2 pills, or more during each DOSE.]*

***[IF PATIENT TOOK ONLY A PORTION OF A DOSE ON ONE OR MORE OF THESE DAYS, PLEASE REPORT THE DOSE(S) AS BEING MISSED.]***

|  | How many doses did you **miss**…  By dose I mean each time you take medications during the day. | |
| --- | --- | --- |
| **Step 1**  Abbreviations / Drug names | **Step 2**  In the last 4 days | **Step 3**  In the last 30 days |
| 1. **__________________________**   ***_____*** *-1. Don’t know*  ***_____*** *-2. Refused* | ____________ doses  ***_____*** *-1. Don’t know*  *_____ -2. Refused* | ____________ doses  ***_____*** *-1. Don’t know*  *_____ -2. Refused* |
| 1. **____________________________**   ***_____*** *-1. Don’t know*  ***_____*** *-2. Refused* | ____________ doses  ***_____*** *-1. Don’t know*  *_____ -2. Refused* | ____________ doses  ***_____*** *-1. Don’t know*  *_____ -2. Refused* |
| 1. **____________________________**   ***_____*** *-1. Don’t know*  ***_____*** *-2. Refused* | ____________ doses  ***_____*** *-1. Don’t know*  *_____ -2. Refused* | ____________ doses  ***_____*** *-1. Don’t know*  *_____ -2. Refused* |
| 1. **____________________________**   ***_____*** *-1. Don’t know*  ***_____*** *-2. Refused* | ____________ doses  ***_____*** *-1. Don’t know*  *_____ -2. Refused* | ____________ doses  ***_____*** *-1. Don’t know*  *_____ -2. Refused* |

G5. Most medications need to be taken on a schedule, such as ‘2 times a day’ or ‘every 12 hours.’ How closely did you follow your specific schedule over the last 4 days?

_____ 0. Never

_____ 1. Some of the time

_____ 2. About half of the time

_____ 3. Most of the time

_____ 4. All of the time

*_____-1. Don’t know*

*______-2. Refused*

G6. *[****Interviewer:*** *Show the participant the drawing and ruler while you are reading the directions.]*

| ***Interviewer Reads:*** “I want to ask about your experience taking your HIV medicines over the past 30 days. Please look at this drawing and ruler. The first cup on the left is empty and represents taking none of your antiretroviral doses in the past 30 days. The last cup on the right is full and represents taking all of your antiretroviral doses in the past 30 days. Using these pictures as a guide, please show me on the line how much of your antiretroviral medicine you took in the past 30 days. For example, if you took half of your doses during the past 30 days, you would select number 5.” |
| --- |

